### Data management

The researchers of this study will adhere to Tehran University of Medical Sciences regulations when storing participant information. To ensure privacy, all records will be anonymized using ID numbers and any identifying participant characteristics data will be securely safeguarded in its database. Access to the login passwords will be restricted to the trial researchers only. The principal investigator entails verifying the accuracy of coding, security, and storage of data, and performing double checks of data entry and data values to ensure accuracy.

### Statistical analysis

Analyses will be performed according to the intention-to-treat analysis (ITT) method. Therefore, all participants who entered the study (regardless of whether they completed the 8-week study period) are included in the analysis. In people who will have a drop, the last data will be used. Then re-analyses will be performed based on the protocol-based analysis method (per protocol analysis), so that the changes in the results can be seen. Patients who finished the 8-week duration of the study and were visited by the researchers will be included in the per-protocol analysis. Descriptive and analytical statistics will be used for data analysis and all analyses will be done in SPSS version 24 software. The normal distribution of the variables will be checked through the scatter plot, histogram, and Shapiro-Wilk test. Variables with non-normal distribution will be reported as median (interquartile range). The mean (standard deviation) will be employed to quantify quantitative variables, while a frequency report (percentage) will be used to characterize qualitative variables. A comparison of absolute or relative frequency is done using the chi-square statistic. Between-group differences in trial results will be evaluated using a general linear mixed model for continuous variables and a chi-square test for categorical variables. Based on this, the significance will be defined in values of *P* less than 0.05 and *q* less than 0.1. Cohen’s changes will be calculated based on the mean and standard deviation, and based on that, the effect size (0.20, 0.50, and 0.80, respectively, low, medium, and high therapeutic effect) of dietary intervention will be determined. Also, a *P*-value < 0.05 will be considered statistically significant in all analyses.

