### Outcome measures

#### Primary outcomes

In the current study, the primary outcome is the changes in health assessment quality (HAQ) score from baseline values.

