#### Secondary outcomes

Secondary outcomes are the changes in erythrocyte sedimentation rate (ESR), C-reactive protein (CRP), disease activity score in 28 joints (DAS-28), Visual Analogue Scale pain intensity (VAS-pain), level of total oxidant and antioxidant capacity (TOC and TAC), oxidative stress index (OSI), tender joint count (TJC), swollen joint count (SJC), tender-swollen joint count difference (TSJD), morning stiffness count (MS), patient global assessment of disease activity (PGA), global assessment of disease activity (EGA), and clinical disease activity index (CDAI) from baseline values.

We will evaluate both primary and secondary outcomes two times, first after the run-in period, at the beginning of the intervention, and second, 8 weeks later.

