### Intervention

The participants in the intervention group follow the IF diet (16:8) in which they are only allowed to receive water and non-energy drinks, tea, coffee, and sugar-free gums for 16 h and 8 h in free consumption mode; they will receive food along with healthy diet recommendations for eight weeks; and the control group will receive their usual diet, along with healthy diet recommendations. To evaluate the level of adherence to the patient’s diet during the intervention, four 24-h food records (including two working days and one day off) will be collected from the patients once every 4 weeks and the physical activity will be checked every 4 weeks using the physical activity registration form and the patients will be asked to record these four physical activities in a way that includes at least two working days and two weekend days. All subjects will be asked in their physical activity not to have any change and medication and its dosage during the study compared to the beginning of the study. If there is a change in the type and dosage of the medicine received, participants will be excluded from the study. For better compliance of participants with the intervention, phone calls will be made with participants every week during the study and possible problems related to compliance with the IF diet will be investigated and necessary guidance will be given. At the end of the intervention, all the evaluations performed at the beginning of the study, including anthropometric indicators, body composition, biochemical evaluations, and questionnaires related to the amount of pain and inflammation in patients with RA, will be evaluated. If adherence to the prescribed diet is < 70% (failure to attend more than 3 phone sessions in a row, or 3 times of non-observance of the fasting diet per week for more than 2 consecutive weeks, changing the type and dosage of drugs received during the study), using new drugs and supplements and changing the dosage of the drugs being used and worsening the disease by the patients, they will be excluded from the study. An announcement to participate in this study will be printed and distributed.

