### Adverse events

We will request that patients inform us of any adverse events that may have taken place during the study period; in case a participant experiences any rare adverse effects from the intervention or decides to discontinue the study for personal reasons, they will be removed from the study.

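### Patients removed after randomisation, including for worsening, are given an HAQ change of exactly zero, so the analysis labelled ITT can be biased in either direction

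*Protocol article*

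**What the plan says.** All references are to the protocol article.

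- **Primary outcomes:** "the primary outcome is the changes in health assessment quality (HAQ) score from baseline values".
- **Secondary outcomes (timing):** "We will evaluate both primary and secondary outcomes two times", at the start of the intervention and 8 weeks later. The contacts in between collect food, activity and compliance data; none is said to collect HAQ.
- **Intervention:** removal after randomisation for drug change, "If there is a change in the type and dosage of the medicine received, participants will be excluded from the study"; for poor adherence, "If adherence to the prescribed diet is < 70% (failure to attend more than 3 phone sessions in a row", with a further criterion on breaking the fast; and for disease activity, "worsening the disease by the patients, they will be excluded from the study".
- **Adverse events:** a participant who "experiences any rare adverse effects from the intervention or decides to discontinue the study for personal reasons, they will be removed from the study".
- **Statistical analysis:** the analysis is called intention-to-treat and includes everyone who entered, completers or not. For those who drop, "In people who will have a drop, the last data will be used". A second, per-protocol analysis uses patients who finished the 8 weeks and were seen.
- **Randomization:** patients, doctors and researchers are not blinded.

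No section says that a removed patient is still assessed at week 8.

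**The concern.** Carrying the last value forward normally assumes some post-baseline value to carry. With only two measurement times there is none, so the rule becomes baseline carried forward and assigns no change to everyone removed.

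Some reasons for removal are themselves outcomes. A patient removed because her arthritis worsened enters the primary analysis as not having worsened. Other reasons are tied to the arm: only the fasting group can break the fast, and the adverse-effect rule refers to effects of the intervention. Because the trial is open-label, judgements about worsening and removal are made with the arm known.

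The primary comparison of a 44-patient trial could thus depend partly on who was removed and why. A week-8 value that was never collected cannot be recovered at analysis.

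**Working it through.** **Inputs.** From the sample size section: SD 0.6 (taken here as the SD of HAQ change), target difference 0.68, 22 per arm, 10% dropout. A negative change is improvement. Assumed, because the documents do not give them: change is normal, worsening means a change above 0.22, and the removal rates below. The plan states no figure for the effect of removal, so there is none to reproduce. (The sample size formula as printed gives 2 × 2.8² × 0.36 / 0.68² = 12.2 per group, not the stated 20. That is a separate matter and does not enter this check.)

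**Step 1: the imputed value.** Last HAQ = baseline HAQ, so change = baseline - baseline = 0.

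**Step 2: no true effect, worseners removed in the fasting arm only.**
- Proportion worsening: P(X > 0.22) = 1 - Φ(0.22/0.6) = 0.357.
- Their contribution to the arm mean: 0.6 × φ(0.367) = 0.224.
- Half removed (0.357/2 = 18% of the arm): bias = -0.224/2 = **-0.11**.
- 10% of the arm removed: bias = -(0.10/0.357) × 0.224 = **-0.06**.
- Simulation (40,000 trials of 22 per arm, t-test): false positives favouring fasting are about **10%** at 18% removal and **5-6%** at 10% removal, against a nominal 2.5%.
- Sensitivity to the assumed threshold, at 10% removal: bias = -0.10 × 0.6 × φ(t/0.6) / (1 - Φ(t/0.6)). This gives -0.05 for t = 0, -0.08 for t = 0.4 and -0.09 for t = 0.6.

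**Step 3: no true effect, same removal rule in both arms.** Both means shift by the same amount. Bias is 0 and simulated two-sided type I error is about 5%.

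**Step 4: true effect -0.68, half of worseners removed in both arms.**
- Control mean: 0 - 0.112 = -0.112.
- Fasting arm: worsening lies (0.22 + 0.68)/0.6 = 1.5 SD above its mean. The contribution is -0.68 × 0.0668 + 0.6 × 0.1295 = 0.032, and half of that is 0.016. The mean becomes -0.696.
- Difference: -0.696 + 0.112 = **-0.58**.

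**Step 5: true effect -0.68, fasting patients removed for reasons unrelated to outcome.** -0.68 × (1 - 0.10) = **-0.61**; -0.68 × (1 - 0.20) = **-0.54**. This works against fasting.

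**Step 6: would replacing the last-data rule be enough?** Take Step 2 with 18% removed and analyse only the observed values: bias = -0.112/(1 - 0.178) = **-0.14**, with about 11% false positives favouring fasting. That is slightly worse than carrying baseline forward. A model that assumes data are missing at random does not correct outcome-related loss when baseline does not predict removal.

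**The case against.** The strongest reply is that the plan keeps everyone in the analysis set, so nobody is dropped from the ITT analysis, and that the worsening and drug-change rules are written for all participants. If they operate alike in both arms and there is no true effect, there is no bias (Step 3). All of this stands. It limits what can be said about size; it does not change how a removed worsener is scored.

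It can also be said that the absence of a week-8 visit for removed patients is inferred. That is correct: the text says they are excluded or removed, and does not say expressly that the visit is cancelled. It is the natural reading, and a last-data rule is needed only for patients whose final value is missing.

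Three stronger readings are tempting, and the documents do not support them.

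- **That the result is biased towards fasting.** This needs worseners to be removed more often in the fasting arm. Open-label conduct makes that possible, but no text states it. The one criterion that clearly applies to a single arm, breaking the fast, produces no false benefit under no effect if it is unrelated to outcome, and dilutes a real benefit (Step 5).
- **That the 18% case is the expected one.** The only loss figure in the protocol is 10%.
- **That imputed zeros always make the SD too small.** In the 18% null case the fasting-arm SD falls from 0.60 to about 0.50. With a true -0.68 and unrelated removal of 10-20%, it stays at about 0.60.

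The per-protocol re-analysis gives some view of sensitivity, but it uses completers and so omits the same patients.

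**Conclusion.** The point holds as a built-in risk of bias in the primary analysis. What follows from the text, on the natural reading that removed patients have no week-8 visit, is that each of them has an HAQ change of exactly zero, including those removed for worsening. The direction and amount of bias depend on who is removed, which the documents do not fix.

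Under the stated assumptions the range runs from no bias, through a spurious benefit of about 0.06 to 0.11 HAQ points, to a loss of about 0.07 to 0.14 points from a true 0.68. It should be settled before follow-up ends, because the missing measurements cannot be obtained afterwards.

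**What to change.** **Intervention and Adverse events sections.** Separate stopping the diet from leaving the study. State that HAQ and all other outcomes are measured at the scheduled week-8 visit in every randomised patient who still consents, whatever the adherence, drug changes, adverse effects or worsening. Clinical care stays with the clinicians. This is the essential change.

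**Statistical analysis section.** Analyse all observed values as randomised. Delete the last-data rule. Use the mixed model already named for values that remain missing. Add one sensitivity analysis that gives patients lost for worsening or adverse effects an unfavourable value, because the change of model alone does not correct outcome-related loss (Step 6).

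**Cost.** Revised wording, a few more week-8 assessments at a visit already planned, and one extra analysis. The primary analysis will include some patients who did not keep to the diet or who changed drugs, which is what an ITT comparison intends.

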### Measuring the adherence to the diet

To encourage adaptation to the IF diet and to have a healthy food intake, during the intervention, all subjects will have weekly and monthly meetings with a nutritionist so that while the intervention group follows the IF diet, all the studied subjects will use the strategies for healthy food intake. In addition, all patients will be given written and verbal instructions for healthy diet recommendations, and as mentioned, there will be no disparity between the participants in the intervention and control groups. Monitoring of the fasting diet is done through the daily interaction of the researcher and the participant in the project (for example, through telephone conversations, taking a 3-day food record). The researcher will hold weekly telephone meetings with all participants to answer questions and check compatibility with the fasting diet in the intervention group. To measure the compliance of the people in the intervention group, if they do not attend more than two phone sessions in a row, or if they do not follow the fasting diet three times a week for more than two consecutive weeks, they are considered non-compliant. In addition, the researcher provides instructions on keeping accurate records of portion sizes and food items to the participants [33].

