### Assessment of food intake

Assessment of food intake through 24-h food recording (including two working days and one day off) will be taken from participants during the intervention at the beginning, weeks 2, 4, 6, and 8. These registers will be taken by an experienced and trained expert and after the process of the data obtained from the food registers, the average intake of food items in these registers will be calculated and will be expressed as grams per day. Then, participants’ nutrient intakes will be calculated by entering these data into Nutritionist4 (N4) software.

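### Conflicting missed-call rules, and a lapse rule that does not track 70% over eight weeks, leave some non-adherent completers in the per-protocol set

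*Protocol article*

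**What the plan says.** Four sections of the protocol article bear on adherence.

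- **Intervention** excludes patients from the study on a rule that begins "If adherence to the prescribed diet is < 70% (failure to attend more than 3 phone sessions in a row". The same bracket continues with "3 times of non-observance of the fasting diet per week for more than 2 consecutive weeks" and ends with "changing the type and dosage of drugs received during the study". The sentence goes on to list new drugs or supplements, dose changes and worsening disease as further grounds for exclusion.
- **Measuring the adherence to the diet** gives a compliance rule for the intervention group only. Its call criterion reads "if they do not attend more than two phone sessions in a row". Its fasting criterion matches the one under Intervention. The stated consequence is a non-compliant label; neither exclusion nor 70% is mentioned.
- **Statistical analysis** puts the intention-to-treat analysis first, with last data carried forward for dropouts. It then adds a per-protocol re-analysis: "Patients who finished the 8-week duration of the study and were visited by the researchers will be included in the per-protocol analysis".
- **Food records**, which Intervention names as the adherence check, are described there as "four 24-h food records (including two working days and one day off) will be collected from the patients once every 4 weeks". Assessment of food intake times them "during the intervention at the beginning, weeks 2, 4, 6, and 8".

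**The concern.** The per-protocol re-analysis is there to show whether the result changes among patients who followed the protocol. For that, the set must be tied to a clear adherence rule. Here two sections disagree on when a patient is non-adherent and on what follows. The rule offered as 70% does not correspond to 70% of the eight-week fasting period. The per-protocol definition refers to neither rule.

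With 22 patients per arm, reclassifying a few can move the per-protocol estimate. The Randomization section says that patients, doctors and researchers are not blinded, so people who know the allocation would be settling the ambiguity.

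**Working it through.** **Inputs.** The intervention lasts 8 weeks, so 8 × 7 = 56 fasting days. Calls are weekly, so about 8. The stated cut is 70%. I read three lapses a week as three or more, and more than two consecutive weeks as at least three.

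**1. Call rule.** More than three in a row means at least 4 missed calls; more than two means at least 3.

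| Longest run of missed calls | Intervention | Measuring the adherence to the diet | Per-protocol set, if week 8 is completed and attended |
|---|---|---|---|
| 2 | not excluded | compliant | in |
| 3 | not excluded | non-compliant | in |
| 4 or more | excluded | non-compliant | out, if removal is carried out |

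The sections disagree at exactly 3. Nor is either call rule a measure of fasting. Missing two, attending one, missing two, attending one and missing two is 6 of 8 calls missed (2/8 = 25% attended), with no run above 2, so neither version triggers.

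**2. What 70% means.** Over the whole period, 0.70 × 56 = 39.2. Below 70% therefore means at most 39 days kept (39/56 = 69.6%), or at least 17 missed. Within one week, 2 lapses leave 5/7 = 71.4% and 3 lapses leave 4/7 = 57.1%. Three lapses is thus the whole-day cut for a *weekly* 70%, and on that reading the protocol's figure is reproduced.

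**3. What the consecutive-weeks condition does.**

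- *Triggers above 70%.* Three lapses in each of three consecutive weeks, with the other five weeks kept, is 9 days missed: (56 − 9)/56 = 83.9%.
- *Does not trigger below 70%.* Every day missed in weeks 1-2 and 4-5, with the rest kept, is 28 days missed: (56 − 28)/56 = 50%. No run of bad weeks exceeds two.
- *Does not trigger, with never more than 3 lapses in a week.* The weekly pattern 3, 3, 2, 3, 3, 2, 3, 3 is 22 days missed: (56 − 22)/56 = 60.7%.

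The rule errs in both directions over the eight weeks. A drug change in the same bracket is not a measure of diet adherence either.

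**4. Who is per-protocol.** The definition asks for completion and a visit. Patients removed under Intervention do not complete, so they drop out of the set. Those who remain in it include the patient with exactly three consecutive missed calls and the 50% and 60.7% patients above, provided they trigger nothing else. Intervention also excludes for worsening disease, so completion depends partly on how the patient fares.

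**5. Food records.** One section collects them every 4 weeks. The other lists the beginning and weeks 2, 4, 6 and 8, which is every 2 weeks. Both cannot be the schedule.

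**The case against.** The strongest reply is that adherence is already screened: patients who meet the Intervention rule leave the study and so cannot finish eight weeks. That is correct, and a reader who infers that the per-protocol set has no adherence content at all goes too far. What stands is narrower: patients non-compliant only under the other section's call rule, and low adherers whose bad weeks are not consecutive enough, remain in.

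A second reply is that the 70% is never defined over 56 days. Read weekly, three lapses is the right cut, and the consecutive-weeks clause adds persistence. In the 84% example the rule would fire at week 3, when the patient has kept 12/21 = 57% of days; the 84% requires the remaining five weeks to be kept. This too stands. It would be wrong to say that the rule has nothing to do with 70%. The failure is over the whole intervention, and the 50% example survives the weekly reading, since four of that patient's weeks are at 0%. Whole weeks off is an extreme pattern, but the 60.7% pattern needs no week worse than three lapses.

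Third, the intention-to-treat analysis comes first, and finer per-protocol criteria may sit in an analysis plan that is not shown. The first part limits the weight of the point. The second does not remove it, because the article states a per-protocol definition and its own sections conflict.

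Finally, a reader might see a further conflict between four food records and three named days. The wording says the records include those days, which need not be exhaustive, so I do not rely on it.

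**Conclusion.** The point holds and should be fixed, but it concerns the supportive analysis. The missed-call thresholds and their consequences differ between sections, with the disagreement at exactly three consecutive misses. The fasting rule fits a weekly 70% cut but not 70% of 56 days: it can catch a patient at 84% and miss one at 50%. Adherence reaches the per-protocol set only through removals. The food-record schedules conflict.

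Three stronger readings are not supported:

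- *A patient can be compliant in one section and excluded in the other.* On the call and fasting criteria the mismatch runs the other way. Anyone excluded for at least 4 missed calls also meets the at-least-3 rule, and the fasting criterion is shared. The conflict is non-compliant in one section and retained in the other.
- *The per-protocol set is simply selected on outcome.* Finishing week 8 is not in itself selection on outcome. The dependence comes from the exclusion for worsening disease, and it is partial.
- *The intention-to-treat set is wrongly defined.* It includes everyone who entered, and the per-protocol definition does not alter it.

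The percentages assume 56 fasting days, 8 calls and the reading of the lapse rule given above. The documents do not say how many patients would show these patterns, so the effect on the estimate cannot be calculated.

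**What to change.** 1. Reconcile the missed-call threshold and its consequence between Intervention and Measuring the adherence to the diet, and the record schedule between Intervention and Assessment of food intake. The investigators must choose which version applies.
2. At each existing weekly call, record on how many of the last 7 days the fast was kept. Define adherence as days kept / 56.
3. State in advance how a missed call is handled. One unrecovered call is 7/56 = 12.5 percentage points, so this choice can decide membership.
4. For intervention patients in the per-protocol set, require at least the protocol's own 70%, which is 40 days or more (40/56 = 71.4%). The 84% patient is then in, if otherwise eligible, and the 50% and 60.7% patients are out.
5. Apply named protocol deviations to both arms, for example the drug changes already listed under Intervention.
6. Use non-adherence to define this set, and keep collecting week-8 outcomes from non-adherers. Outcomes are measured only at the start and at week 8, so a patient removed without a final visit has only the baseline value to carry forward in the intention-to-treat analysis.
7. Report the per-protocol result as supportive.

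The cost is one definition, one question in a call already planned, and week-8 visits for patients who would otherwise have been removed. The downside is a possibly smaller per-protocol set.

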## Methods

### Study design and participants

In this randomized, controlled, parallel-group superiority trial, we compare the effects of the IF diet to the usual diet on clinical symptoms, inflammation, and oxidative stress in overweight and obese postmenopausal women who suffer from RA with the diagnosis of a rheumatologist and by the criteria of the American College of Rheumatology (ACR) over 8 weeks, with a 1:1 allocation ratio, in 2023–2024. This study will be conducted on eligible patients who will be referred to the rheumatology clinics of the Tehran University of Medical Sciences. Participants will be randomly allocated into a control group with the usual diet, and an intervention group with the IF diet. The protocol of this study was approved by the Ethics Committee of Tehran University of Medical Sciences (IR.TUMS.IKHC.REC.1401.376) and was registered at the Iranian Registry of Clinical Trials (IRCT20230217057441N1). After explaining the objectives of the study and the method of its implementation, documented informed assent is obtained from the attendees (Fig. 1).

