### Randomization

Participants will be randomized using stratified permuted blocks. A block size of 4 will be used, and stratification factors are the participant’s BMI (between 25 and 30 and 30 and 35 kg/m^2^) and whether they are receiving biological or non-biological drugs. People will be allocated to one of the two groups of intervention and placebo. Random allocation will be based on a random number list; the letters A and B will be assigned to an equal number of random number list. In this study, patients, doctors, and researchers are not blinded.

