### Run-in period

Before starting the intervention, the selected people first will be entered into a 2-week run-in period to collect enough information about their food habits and intake. Then, by using a general information questionnaire about age, gender, education level, history of diseases and hospitalization, surgery, and history of taking drugs, supplements will be taken from all people. During this period, patients will complete a 24-h food record for 3 days including two working days and one day off per week, and questions will be asked about their eating habits. Before the intervention, anthropometric measures such as height, weight, waist circumference, and body composition, as well as biochemical evaluations including TOC, TAC, CRP, and ESR, will be measured and questionnaires related to the pain and inflammation will be collected. At the end of the run-in period and before the commencement of the intervention, people will be divided into blocks based on their BMI and medications received.

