### Study sample size calculation

Considering that the primary goal in this study is to improve clinical symptoms in the IF group compared to the normal diet (HAQ score is considered as the primary outcome in this study), the number of samples required to conduct this study based on the change in HAQ, the IF group compared to the usual diet by 0.68 (a minimum clinically important difference), and considering the test power of 80%, the type I error is equal to 0.05, and the standard deviation is 0.6 was calculated for the result of 20 people in each group. We used SPSS software for calculation.$$n=2\times \frac{{\left({z}_{1-\frac{\alpha }{2}}+{z}_{1-\beta}\right)}^2}{\Delta ^2}\ S2$$$${n}=2\times \left[{\left(1.96+0.84\right)}^2\times \right(\left(0/{6}^2\right)\Big]/{(0.68)}^2$$

*n* = sample size in each group

*a* = type I error = 0.05

*b* = Power = 0.80

*S*
^2^ = standard deviation of the studied result (SD)

Δ^2^ = minimal clinically important difference

Therefore, considering a 10% chance of dropping out, the final sample size will be 44 people (22 people in each group) [54].

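### The planned mixed model names neither baseline HAQ nor the two randomisation strata; without them it reduces to an unadjusted, less precise change-score comparison

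*Protocol article*

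**What the plan says.** All references are to the protocol article.

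- **Primary outcomes:** "the primary outcome is the changes in health assessment quality (HAQ) score from baseline values". The Secondary outcomes section also defines its measures as changes from baseline.
- **Secondary outcomes (timing):** "We will evaluate both primary and secondary outcomes two times", once after the run-in and once eight weeks later.
- **Randomization:** "Participants will be randomized using stratified permuted blocks", with block size 4. The factors are BMI class (25–30 and 30–35 kg/m²) and "whether they are receiving biological or non-biological drugs". The Run-in period section repeats this: "people will be divided into blocks based on their BMI and medications received".
- **Statistical analysis:** "Between-group differences in trial results will be evaluated using a general linear mixed model for continuous variables". No response form, fixed effect, random effect or covariate is given. The main analysis is by intention to treat with the last value carried forward. The per-protocol set is limited to patients who finished the eight weeks.
- **Study sample size calculation:** the plain two-sample formula is applied to the change in HAQ, with no term for a baseline correlation or a covariate.
- **Strengths and limitations:** balancing the arms on variables that could influence the results is listed as a strength.

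**The concern.** The trial measures HAQ at baseline and balances the arms on two factors that its authors think may matter. The analysis sentence mentions neither. If the model is fitted as worded, two things follow.

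1. A change score subtracts the whole baseline value, whereas the best linear prediction of the week-8 value uses only a fraction of it. Any chance baseline difference between arms is over-corrected, and this adds variance. With about 20 evaluable patients per arm, such differences are to be expected.
2. Stratified randomisation removes between-stratum variation from the treatment contrast. A model without the strata leaves that variation in its residual, so its standard error describes a less well balanced trial than the one that was run.

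What is at stake is the width and calibration of the primary confidence interval in a small trial.

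**Working it through.** **Inputs from the article:** two visits; 1:1 allocation; 20 evaluable per group (22 randomised); SD 0.6; target difference 0.68; two-sided alpha 0.05. **Assumed, because not given:** baseline to week-8 correlation r of 0.5–0.8 with equal variances at the two visits; share R² of residual variance explained by the strata of 5–20%; and 0.6 taken as the SD of the change.

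**The plan's own figure.** 2 × 2.8² × 0.6² / 0.68² = 12.2, so 13 per group, not 20. Reading 0.6 as a variance gives 2 × 2.8² × 0.6 / 0.68² = 20.3. That is a separate matter and the present point does not depend on it, but it affects the power figures used under the objection.

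**Step 1: what the model estimates.** With only two visits, the last value available for a dropout is the baseline value. Every patient in the intention-to-treat set therefore has a complete pair, and so does every completer in the per-protocol set. With complete pairs and a free mean for each arm at each visit, the group-by-time term of a mixed model is

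(week-8 mean − baseline mean) in the fasting arm − (week-8 mean − baseline mean) in the control arm.

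This is the unadjusted difference in mean change. Using change itself as the response, without covariates, gives the same estimate. The result differs only if baseline is a covariate or the two baseline means are constrained equal.

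**Step 2: baseline.** With visit variance σ², change has variance 2σ²(1 − r) and the baseline-adjusted response has variance σ²(1 − r²). Their ratio is (1 − r²) / [2(1 − r)] = (1 + r)/2. At 20 per group the change-score SE is 0.6 × √(2/20) = 0.190, with 95% half-width 1.96 × 0.190 = 0.37.

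| r | variance ratio | reduction | adjusted SE | half-width |
|---|---|---|---|---|
| 0.5 | 0.75 | 25% | 0.164 | 0.32 |
| 0.7 | 0.85 | 15% | 0.175 | 0.34 |
| 0.8 | 0.90 | 10% | 0.180 | 0.35 |

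**Step 3: strata.** With balanced strata, leaving them out inflates the SE by 1/√(1 − R²): 1.026, 1.054 and 1.118 for R² = 0.05, 0.10 and 0.20.

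A simulation checked this: 44 patients, four equally likely strata, blocks of 4, SD 0.6, 6,000 runs per setting, ordinary linear model with and without the two factors.

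| R² | model SE, no strata | model SE, strata | type I, no strata | type I, strata |
|---|---|---|---|---|
| 0 | 0.180 | 0.180 | 4.6% | 4.7% |
| 0.10 | 0.180 | 0.171 | 4.0% | 5.3% |
| 0.20 | 0.181 | 0.161 | 3.1% | 5.3% |

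The ratios of the model SEs agree with the formula. Against the actual spread of the unadjusted estimate (0.1724 and 0.1653 at R² of 0.10 and 0.20), the unadjusted model SE is too large by 0.1798/0.1724 = 1.04 and 0.1806/0.1653 = 1.09. These are slightly below the formula because unfinished blocks leave some imbalance.

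**The case against.** **Silence is not exclusion.** The article names a class of model and lists no terms. It condenses a fuller protocol, which it says is available through the registry and which is not shown here. A reader might infer that the plan has decided to leave out baseline and strata. Nothing in the text says so, and this objection stands in full.

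**A change-score outcome is compatible with adjustment.** Regressing change on treatment and baseline gives the same treatment effect and standard error as regressing the week-8 value on the same terms. A mixed model with a common baseline mean also uses baseline. Both fit the wording, so the outcome definition alone proves nothing. But neither is stated, and Step 1 shows that the model without such a term does not recover the precision.

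**The loss is one of efficiency.** A reader might also infer bias or false positives. Under randomisation the change-score difference is unbiased, and ignoring prognostic strata pushes type I error below 5%, not above it. This stands too.

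**Power looks ample.** With SD 0.6, a difference of 0.68 and 20 per group, power is already 94.8%; adjustment gives 98.5% (r = 0.5) or 96.5% (r = 0.8). That comfort depends on reading 0.6 as an SD. If 0.6 is the variance, which is the reading that comes close to 20 per group, the SE is √(0.6 × 2/20) = 0.245 and power is Φ(0.68/0.245 − 1.96) = 79%. With adjustment the SE is 0.212 or 0.232, and power is 89% or 83%.

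**Conclusion.** The point holds as a conditional one. The stated analysis names neither baseline HAQ nor the two strata. Given two visits and carried-forward values, it is an unadjusted change-score comparison unless a baseline covariate or a baseline constraint is added.

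The cost of the baseline part is a variance that adjustment would lower by 25% to 10%, for an assumed r of 0.5 to 0.8 and equal variances. The strata part is a standard error about 3–12% too large, if the strata explain an assumed 5–20% of residual variance, and zero if they explain none. The article's own remark that the balanced variables may influence the findings makes some effect plausible but does not give its size. The two gains should not simply be added, because strata and baseline HAQ may explain some of the same variation.

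The documents do not support the stronger claims that the terms are deliberately omitted, that the intervals are certainly wrong, or that the treatment estimate is biased. The change is worth making before analysis, with moderate confidence as to the size of the gain.

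**What to change.** State the primary model: week-8 HAQ-DI (or its change) on treatment, baseline HAQ-DI, BMI stratum as used in randomisation, and biological treatment (yes/no). The equivalent is a mixed model on both visits with the arms' baseline means constrained equal and the two strata as covariates. Report the adjusted difference between arms with its 95% confidence interval. Use the same form for each continuous secondary outcome, with that outcome's own baseline.

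The cost is a sentence in the analysis plan and three degrees of freedom: with all 44 patients in the regression form, residual degrees of freedom go from 42 to 39. All the variables are already collected, so neither the sample size nor the visit schedule changes. If the fuller protocol or analysis plan already specifies these terms, it is enough to say so and to cite the model there.
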